### Study procedure

Table 2 outlines the schedule of enrolment, interventions and assessments. Patients will undergo baseline chest X-ray and ultrasound assessment. QoL and symptom data will be collected using the EORTC QLQ-C30 questionnaire, MRC Dyspnoea Scale and 100 mm Visual Analogue Score (VAS) for pain and breathlessness. These questionnaires will be repeated for both groups during each follow-up visit.

**Table 2 BMJOPEN2016012795TB2:** Schedule of enrolment, interventions and assessments

	Both groups	Usual care group					IPC group					
Study procedures	Consent/baseline	Postrandomisation	Days 2–5	Day 7	Day 14	Day 30, 60, 90	Postrandomisation	Day 4	Day 7	Day 14	Day 30, 60, 90	Ongoing (between follow-up)
Sign consent	X											
Demographics/medical history/blood pressure	X											
Randomisation	X											
Local anaesthesia		X					X					
Ultrasound-guided IPC or chest drain insertion		X					X					
Pleural manometry		X					X					
Daily observations (HR, respiratory rate, oxygen requirement, BP, chest drain assessment) drain in situ			X									
Inpatient drainage			X									
Community drainages												X
Drainage booklet							X					X
Pleurodesis			X					X				
Drain removal			X							X		
AE data collection		X	X	X	X	X	X	X	X	X	X	X
Chest X-ray	X	X	X	X	X	X	X	X*	X	X	X	X
Thoracic ultrasound	X			X	X	X		X	X	X	X	
VAS assessment (pain and breathlessness)	X			X	X	X			X	X	X	
EORTC QLQ -C30	X			X	X	X			X	X	X	
MRC Dyspnoea Score	X			X	X	X			X	X	X	
WHO performance status	X											

*Optional CXR based on USS appearances.

AE, adverse events; CXR, chest X-ray; IPC, indwelling pleural catheter; MRC, Medical Research Council; USS, ultrasound scan.

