## Objectives

### Hypothesis

The primary hypothesis is that outpatient management of MPEs with an IPC improves global health-related QoL at 30 days following insertion when compared to standard treatment according to BTS guidelines.

With no validated QoL assessment tools for patients with MPE, global health-related QoL as measured by the EORTC QLQ-C30 has been selected as the primary outcome measure. It is an extensively used tool and validated for malignant disease of various histological types.^14^ Using one tool to assess health-related QoL will ensure that the protocol limits the burden to trial participants.

Primary and secondary objectives and outcome measures are summarised in table 1.

**Table 1 BMJOPEN2016012795TB1:** Primary and secondary objectives for the OPTIMUM trial

Objectives	Outcome measures	Time points of evaluation
*Primary objective*		
To assess whether a minimally invasive evidence-based pathway for the outpatient management of malignant pleural effusion improves global health-related quality of life at 30 days	Self-reported health-related quality of life based on EORTC QLQ-C30 questionnaire	Day 30
*Secondary objectives*		
Improvement in global health-related quality of life at 60 and 90 days	Self-reported health-related quality of life based on EORTC QLQ-C30 questionnaire	Day 60, 90
Pleurodesis failure rate	Subsequent pleural intervention required on the same side as pleurodesis Chest X-ray opacification greater than 25% on side of intervention judged by two independent clinicians	Day 30, 60, 90
Improvement in symptoms of pain and breathlessness	Medical Research Council (MRC) Dyspnoea Scale 100 mm Visual Analogue Scale for pain and breathlessness	Day 30, 60 and 90
Complication rate	Clinical review and adverse event documentation	Day 7, 14, 30, 60 and 90

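### Between-visit adverse event collection is scheduled for the IPC arm only, so the secondary complication-rate comparison may partly reflect unequal ascertainment

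*Protocol article*

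**What the plan says.** Table 2 (Study procedure) has one shared baseline column, five usual-care columns and six IPC columns. The sixth IPC column, "Ongoing (between follow-up", has no usual-care counterpart. It is marked for community drainages, the drainage booklet, the row "AE data collection" and chest X-ray. It is not marked for ultrasound, the visual analogue scales, the QLQ-C30 or the MRC score. No start or end is given for it.

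Usual care has its own extra row, "Daily observations (HR, respiratory rate, oxygen requirement, BP, chest drain assessment) drain in situ", marked for days 2–5 only.

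Table 1 (Objectives) lists the complication rate as a secondary outcome, measured by "Clinical review and adverse event documentation" at "Day 7, 14, 30, 60 and 90", without distinction by arm. Pleurodesis failure is assessed at days 30, 60 and 90 and has two components: "Subsequent pleural intervention required on the same side as pleurodesis" and "Chest X-ray opacification greater than 25% on side of intervention judged by two independent clinicians".

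Recruitment and randomisation states that neither patients nor the research team are blinded. Adverse event reporting sets out how known events reach the sponsor. It makes no distinction by arm and gives no collection interval.

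**The concern.** The complication outcome is whatever gets documented as an adverse event. If one arm has a standing channel for documenting events between visits and the other relies on visits alone, more of the same underlying events can be recorded in the first arm.

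In usual care the gaps between scheduled contacts after day 14 are 16, 30 and 30 days (14 to 30, 30 to 60, 60 to 90). Several of the events listed under Expected AEs are minor, such as drain-site pain, local bleeding, local infection and fever, and may be forgotten by the next visit. IPC patients keep a drainage booklet, and Exclusion criteria rules out patients for whom drainage at least twice a week cannot be provided, so the IPC arm has regular occasions on which an event can be noted.

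At stake is the fairness of the safety comparison between the outpatient and inpatient pathways. After discharge, the likely direction is against the IPC pathway. The analysis can discard IPC events that came from the extra channel, but it cannot recover usual-care events that were never collected.

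**Working it through.** **Step 1. Count the marks after baseline in Table 2, and compare them with the outcome days in Table 1.**

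| Item | Usual care | IPC |
|---|---|---|
| Columns after baseline | 5 | 6 |
| Adverse event collection, columns marked | 5 | 6 |
| Chest X-ray, columns marked | 5 | 6 (day 4 optional) |
| Adverse event collection at days 7, 14, 30, 60, 90 | 5 visits | 5 visits |
| Chest X-ray at days 30, 60, 90 | 3 visits | 3 visits |

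Scheduled visits are equal in both arms. The unequal count comes from the IPC-only between-visit column. The table footnote, "Optional CXR based on USS appearances", concerns the IPC day-4 film and has no bearing on days 30 to 90.

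**Step 2. Does the extra column reach an outcome?**

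- Complications: it can. The measure is adverse event documentation, and nothing in the article keeps events from the IPC-only column out of the rate.
- Opacification: no. It is assessed at days 30, 60 and 90, and both arms have a film at each.

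**Step 3. The plan's own figure.** The stated sample size is 71 per arm. The adjusted SD is 23.60 × √(1 − 0.49) = 16.85. The noncentrality is 142 × 0.25 × 8² / 16.85² = 8.0. The F test on 1 and 139 degrees of freedom then has power 0.802, so the stated figure reproduces. It concerns the primary outcome and is used here only to supply 71 per arm.

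**Step 4. Possible size.** The article gives neither a complication rate nor a detection rate, so all values here are assumptions. Let p be the true rate, equal in both arms, and let s be the share of events detected in usual care, with complete detection in the IPC arm. The spurious difference is p − p × s = p × (1 − s). The table gives it in percentage points. In brackets is the probability that a two-sided 5% comparison of proportions with 71 per arm declares more complications with IPC; the nominal value in that direction is 0.025.

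| True rate p | s = 0.90 | s = 0.80 | s = 0.70 |
|---|---|---|---|
| 0.10 | 1 (0.039) | 2 (0.061) | 3 (0.093) |
| 0.20 | 2 (0.049) | 4 (0.090) | 6 (0.156) |
| 0.30 | 3 (0.059) | 6 (0.124) | 9 (0.232) |
| 0.40 | 4 (0.071) | 8 (0.166) | 12 (0.325) |

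Of 71 patients, 1 to 12 points is about 1 to 9 patients (71 × 0.01 = 0.7; 71 × 0.12 = 8.5). If IPC detection is also incomplete, only the gap in detection matters. With p = 0.25, 95% detection in IPC and 80% in usual care, the observed rates are 23.75% and 20%, a difference of 3.75 points.

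**The case against.** The strongest reply is that Table 1 already sets common days for complications and Table 2 marks adverse event collection for both arms on each of them. A visit can also pick up events since the previous one. This stands in part: it makes the bias a risk, not a certainty. But the article neither says that visits look back in this way nor reconciles the common days with the extra IPC source.

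A second reply is that Adverse event reporting treats both arms alike. It does, and it is therefore too strong to say that nothing between visits could be recorded in usual care: a related or unexpected serious event must be reported once known. But that section governs events already known. It does not equalise how they are found.

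A third reply is that the column simply belongs to having a catheter in place. The usual care group section allows an IPC to be considered later in patients with trapped lung, yet usual care has no such column. The IPC column, in turn, has no stated end.

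A fourth reply is that the full protocol or case report form, not shown here, may ask both arms the same question. That is possible, and it would settle the point.

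Two stronger readings are tempting. A reader might infer that the opacification component of pleurodesis failure is also biased. Table 1, Table 2 and both pathway descriptions rule this out, because both arms have films on all three assessment days. At most, an extra IPC film might prompt an earlier re-intervention, and the article does not show that it would. A reader might also infer continuous IPC capture over the 76 days from day 14 to day 90. The column has no stated duration and the catheter may be removed at day 14, so that figure has no support.

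**Conclusion.** The point holds for the complication rate. As published, the schedule gives the IPC arm an adverse event channel between visits that usual care lacks, and the article does not say whether what it yields enters the comparison. After discharge the probable direction is against IPC.

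The size cannot be derived from the document. The range of about 1 to 12 percentage points rests on assumed true rates of 10% to 40%, complete detection in IPC and 70% to 90% detection in usual care. It illustrates the possible bias and does not estimate it.

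The closer observation of usual-care inpatients on days 2–5 works the other way. It is part of the pathway under comparison and not a planning error, and there is no ground for assuming that the two effects cancel.

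Only a secondary outcome is touched. The day-30 QLQ-C30 primary outcome, the sample size of 142 and the opacification readings are unaffected. The correction is worth making because it is cheap and because missed events cannot be recovered later.

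**What to change.** In Table 2, mark between-visit adverse event collection for usual care as well, from discharge to day 90, and state that the IPC column covers the same period. At each visit, ask both arms the same question about events since the last visit. State that the between-arm complication rate counts events from sources common to both arms over the same window. Events known only through an IPC-specific source, such as the drainage booklet, can be reported separately.

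The cost is one added entry in the schedule, a prompt on the case report form and a little more adverse event recording in usual care. Sample size, primary analysis and patient management do not change.

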### The indwelling pleural catheter group

The IPC intervention algorithm is summarised in figure 1. Patients allocated to the IPC group will undergo chest ultrasound to assess the pleura, pleural fluid and to identify a safe site for insertion.

**Figure 1 BMJOPEN2016012795F1:**
[figure not shown]
Trial pathway for the indwelling pleural catheter group. CXR, Chest X-ray; USS, ultrasound scan; IPC, indwelling pleural catheter; QoL, quality of life.

The IPC will be inserted as per normal practice.^9^ Once the indwelling catheter is inserted, intrapleural pressure will be measured with a water manometer (Medifix Manometer Scale, B. Braun, Sheffield, UK), and an attempt will be made to evacuate as much fluid as is tolerated while monitoring the patient's symptoms and oxygen saturation. Serial measurements of pleural pressure will be recorded for every 500 mL of fluid drained continuing drainage until one of three criteria is met:
Effusion fully drained.Patient symptomatic with pain, cough or presyncope.End expiratory pleural pressure drops below 20 cm H_2_O or pleural elastance >10 (pleural elastance is calculated by dividing the change in pleural pressure by the volume (in litres) removed).

A postinsertion chest X-ray will be performed to confirm the position of the catheter. Patients will be discharged, and a district nurse referral completed if required. Patients on steroids will be asked, if clinically possible, to discontinue steroids 48 hours prior to their visit on day 4 given the potential for talc slurry. In steroid-dependent patients, admission to hospital prior to pleurodesis will be at the discretion of the clinician as per standard practice.

Patients will be reviewed on day 4 (±24 hours) postprocedure. The pleural fluid will be drained via the IPC. The quantity of fluid removed, and re-expansion of lung will be assessed. If the average pleural fluid output is low (<150 mL/day) and if satisfactory re-expansion of lung is confirmed by ultrasound, talc pleurodesis will be attempted through the IPC.

Satisfactory lung re-expansion will be defined as lung sliding on the chest wall in at least five of six defined areas in the chest (figure 2). In the case of uncertainty, chest radiographs will be used. A diagnosis of lung entrapment can be made using the pleural manometry data, ultrasound and chest radiograph appearances. For example, if uncertainty exists over potential small areas of entrapment on ultrasound and the X-ray appearances are satisfactory, talc may be administered.

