### Study population

A total of 142 patients in participating respiratory departments meeting the eligibility criteria will be recruited. All sites have a dedicated pleural service with experience in IPC insertion.

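### The end-expiratory pressure limit for stopping drainage at IPC insertion is printed without a minus sign; read literally as +20 cm H2O, it does not work as a lower safety floor

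*Protocol article*

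**What the plan says.** The article's section on the IPC group describes drainage at catheter insertion in the text that follows the figure 1 legend. The aim is that "an attempt will be made to evacuate as much fluid as is tolerated", with symptoms and oxygen saturation monitored. Pressure is read at fixed volumes: "Serial measurements of pleural pressure will be recorded for every 500 mL of fluid drained". Drainage goes on "continuing drainage until one of three criteria is met", so any one of the three is enough to end it.

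The first two criteria are complete drainage and the onset of symptoms. The third has two limbs. One is "End expiratory pleural pressure drops below 20 cm" H2O, with no sign before the number. The other is a pleural elastance above 10, where "pleural elastance is calculated by dividing the change in pleural pressure by the volume (in litres) removed".

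The limit appears nowhere else in the text. The usual care section says that manometry is recorded but gives no pressure limit. Figure 1 could hold the value ("The IPC intervention algorithm is summarised in figure 1"), but the figure is not shown.

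**The concern.** The third criterion is worded for a pressure that falls as fluid is removed, and it sits beside a limit on how steeply it falls. Both features describe a lower floor that acts late in drainage, when pressure has become markedly negative. An unsigned 20 does not describe such a floor. Taken as +20, the criterion would already be satisfied at or near the start of drainage in any patient who does not open well above 20 cm H2O. The complete-drainage and symptom criteria would then rarely be the ones that act.

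This is the only absolute pressure limit the article gives for the experimental procedure. The same section also allows the manometry readings to contribute to a diagnosis of lung entrapment, so a rule that ended drainage early would also shorten that record. The article invites further centres to join, so staff at a new site may read the limit here.

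**Working it through.** The printed limit is a clinical threshold. It is not derived from other figures in the article, so there is no plan figure to reproduce. The check is whether the rule behaves as a floor under each sign.

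**Inputs from the article (IPC group section).** Limit printed as 20 cm H2O, unsigned; readings every 0.5 L; elastance E = pressure change per litre removed, with a stop above 10.

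**Assumed inputs.** Opening pressure P0 from 0 to 25 cm H2O, and E of 2, 5 and 10 cm H2O per litre. The article gives no opening pressures.

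**Formula.** From the article's definition, E = (P0 - P)/V, so P = P0 - E × V after V litres.

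**Step 1: limit read as +20.** At the first reading V = 0.5, so P = P0 - 0.5 × E.

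| P0 | P at E = 2 | P at E = 5 | P at E = 10 | Below +20 at 0.5 L? |
|---|---|---|---|---|
| 0 | -1 | -2.5 | -5 | yes |
| 5 | 4 | 2.5 | 0 | yes |
| 10 | 9 | 7.5 | 5 | yes |
| 15 | 14 | 12.5 | 10 | yes |
| 20 | 19 | 17.5 | 15 | yes |
| 25 | 24 | 22.5 | 20 | no |

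For every P0 at or below 20 and any positive E, P0 - 0.5 × E is less than 20, so the stop is met by the first reading. For P0 below 20 it is already met before any fluid is removed. Only above 20 does the literal rule leave room to drain: from P0 = 25 the pressure reaches 20 after (25 - 20)/E litres, which is 1.0 L at E = 5 and 0.5 L at E = 10.

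**Step 2: limit read as -20.** Pressure reaches the limit after (P0 + 20)/E litres. The smallest volume arises at E = 10, the steepest fall that the elastance limb still permits:

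- P0 = 0: (0 + 20)/10 = 2.0 L
- P0 = 10: (10 + 20)/10 = 3.0 L
- P0 = 20: (20 + 20)/10 = 4.0 L

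These are not expected drained volumes, since complete drainage or symptoms may come first. They show only that -20 acts late and leaves the other criteria room to operate, as a floor should.

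**Step 3: reach of the point.** The sample size section uses a difference of 8 points, an SD of 23.60, an R² of 0.49, 80% power and a 5% level. None of these depends on the drainage limit.

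**The case against.** The strongest objection is that the point rests on one character in text that a program read from a PDF. No negative number is printed anywhere else in the article, so there is no direct test of whether minus signs survived. Other symbols did survive: ± and < in the same section and ≥ in the randomisation section. A lost sign is therefore possible but not the likelier explanation. The caveat stands, and it is why the remedy begins with a check.

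Context also points a careful reader to the intended value. The article states that "All sites have a dedicated pleural service with experience in IPC insertion", and such operators would probably act on -20. Fluid is also drained again at the day 4 review, so a short first drainage would be partly made good. This stands too, and it keeps the practical risk low. It does not make the printed number right.

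Two stronger readings are tempting. A reader might infer that a +20 limit flatly conflicts with the aim of removing all the fluid the patient can tolerate. The text does not support that, because the aim is expressly bounded by the three stopping criteria. A stop rule that bites too early defeats its own purpose, but it is not logically inconsistent with an aim made subject to it.

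A reader might also infer that patients who open below 20 have no pressure protection, by taking the wording to require a crossing of +20 from above. That reading is strained. Any large negative pressure computed from it would rest on assumed opening pressures, and it would need the elastance, symptom and complete-drainage stops all to stay silent.

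**Conclusion.** The point holds as a minor procedural-safety correction, with medium confidence. As printed, the limit has no sign. Read literally as +20, it would be met by the first 500 mL reading in every patient opening at or below 20 cm H2O. That size rests on the assumed opening pressures; the literal rule would leave some room for drainage in a patient opening well above 20. The value -20 is inferred from the falling-pressure wording and the elastance limit beside it, and nothing in the text shown states it.

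It should not be inferred that the trial was run to a wrong limit. The approved protocol and figure 1 are not shown, and either may carry the correct value. There is no consequence for sample size, power, the primary endpoint or its analysis.

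**What to change.** Check the limit against the approved protocol and figure 1. Once confirmed, print it in the article as *below -20 cm H2O*. If the approved protocol has the same omission, correct it there and send sites a short notice.

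The cost is one document check and a one-character correction, plus the notice if it is needed. Nothing in the statistical design changes.

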**Figure 2 BMJOPEN2016012795F2:**
[figure not shown]
Sites of thoracic ultrasound to assess for pleural apposition.

If the lung has not re-expanded, continued regular drainage (depending on fluid output) will be advised.

If talc pleurodesis is attempted based on the above criteria, this will be administered as a ‘slurry’ via the IPC. Then, 3 mg/kg (max 250 mg) 1% lignocaine will be instilled into the pleural space via the IPC to prevent any acute pain. This will be followed by 4 g of talc mixed with 50 mL normal saline via the drain followed by 50 mL normal saline flush. Patients will be observed for at least 1 hour following talc instillation.

The patient will then be sent home with the advice to drain daily with a 1 L vacuum bottle for 3 days. This can be performed by themselves, their carer or district nurse. They will be reviewed on the third day postpleurodesis (+48 hours). They will be asked to complete health-related QoL and symptom questionnaires and undergo ultrasound and chest X-ray review of the pleural collection.

If there is no recurrence of effusion with satisfactory ultrasound evidence of pleural symphysis in at least five out of six areas, patients will be advised not to undertake any drainage for further 7 days. On day 14 (±24 hours) postintervention, they will undergo QoL and symptom questionnaires, ultrasound and chest X-ray review. If pleurodesis is successful, the IPC will be removed.

Successful pleurodesis will be defined as pleural symphysis in at least five out of six areas (see figure 2) on ultrasound as evidenced by the absence of lung sliding in these areas.

Patients will undergo a clinic review at 30, 60 and 90 day's postprocedure. At each visit, a chest X-ray and chest ultrasound scan will be performed recording X-ray appearances and the presence of pleural thickening, depth of effusion and extent of septations on ultrasound. Patients will be required to complete the EORTC QLQ-C30 questionnaire, MRC Dyspnoea Scale and VAS for pain and breathlessness.

### The usual care group

The usual care pathway is summarised in figure 3. Patients randomised to the usual care group will be managed according BTS guidelines. They will be admitted to hospital for drain insertion and undergo a thoracic ultrasound to assess the pleura, pleural fluid and to identify a safe site for insertion. A standard 10 French—14 French gauge chest drain will be inserted. Fluid will be emptied gradually measuring oxygen saturations and monitoring for symptoms. Pleural manometry will be recorded.

